### Sample size estimation

In this study, sample size was estimated for each of the two treatment groups considering a minimum power of 0.80 (type II error rate) at a two-sided 0.05 significance level (type I error rate). A previous single-group clinical trial that assessed the incremental effect of the SIMO treatment compared to the CD, and considered the outcome satisfaction with the dentures and OHRQoL, served as the data source for this sample size estimation [23]. A minimum of 24 patients will enter this two-treatment parallel-design study, considering that the true difference between treatments is 7.4 units for OHIP-EDENT and 2.6 units for satisfaction scores, assuming unequal variances for both groups. An increase of 10 % to reduce the impact of loss to follow-up on study power resulted in a minimum final sample of 28 participants, 14 in each treatment group.

### Randomization

A computer-based random number generator will be used to assign participants into the treatment groups [24]. In order to prevent imbalance between groups, participants will be stratified according to gender [25]. Block randomization will be used to randomly assign participants to sets of different sizes, using unsorted numbers with a range from 1 to 2 (representing the two treatments) and an allocation ratio of 1:1 for the control and experimental groups. The sequence will be concealed in opaque, consecutively numbered envelopes for each block. After each enrollment, the next randomization envelope will be opened, according to the previously established sequence. An independent collaborator will manage the allocation and inform participants about their assigned groups.

If a participant allocated to the SIMO group refuses to receive the implant treatment (noncompliance), follow-up will occur the same way as in the control group. Moreover, intention-to-treat analysis will be performed, which means that during statistical analysis noncompliant participants will be kept in their original group, even if they did not receive the allocated treatment. This may provide a more conservative estimation of treatment effect, minimizing the probability of type I error occurrence [26].

### Masking/blinding

To avoid selection bias and ensure adequate allocation concealment, their treatment group will only be revealed for each participant after the assessment of the baseline outcomes, which will occur after the delivery and regular use of the new set of conventional dentures. Since full blinding for the two interventions is not possible for those involved with treatment management and collection of data, only those collecting and analyzing clinical data from masticatory performance tests will be unaware of the assigned treatment.

### Interventions

#### Control group (complete denture treatment)

New maxillary and mandibular dentures will be fabricated following a standardized protocol. Clinical steps will include: (1) anamnesis and preliminary impression with alginate (Jeltrate Dustless, Dentsply, Brazil) using stock trays, (2) final impression with a custom tray and zinc oxide eugenol impression material (Lysanda, Lysanda Produtos Odontológicos Ltda., São Paulo, Brazil), (3) occlusal registrations and mounting in a semiadjustable articulator fixed in average settings, without the use of a facebow, (4) a try-in visit to assess the artificial teeth (Trilux, Dental Vip Ltda, Pirassununga, São Paulo, Brazil), (5) delivery of the dentures and (6) visits for adjustment. All laboratory procedures will be carried out by the same dental technician using standard procedures for complete denture processing.

Moreover, the dentures will be technically evaluated by an experienced prosthodontist in order to guarantee maximum quality according to each case. When needed, retreatment or any adjustment/repair in the dentures will be performed accordingly. Participants will receive regular maintenance for their dentures, including adjustments for elimination of sore areas, denture relining and repair of fractures, when needed, until the end of the follow-up period.

#### Experimental group (single-implant mandibular overdenture (SIMO))

##### Prosthodontic phase

All prosthodontic procedures for construction of conventional maxillary and mandibular dentures will be performed similarly to the control group.

##### Presurgical procedures

After insertion and adjustment of the new dentures, implant placement surgery will be planned with the aid of panoramic and lateral cephalometric radiographs, which will serve to determine implant dimensions and position, as well as to assess the conditions of the implant bone site. A cephalometric radiograph will be acquired with the dentures in situ and, to make the proposed implant position evident, a thin strip of lead foil will be fixed outlining the outer surface of the lower denture in the midline position [11]. Imaging exams should confirm the presence of sufficient bone volume for the placement of an implant with a length of at least 8 mm.

In order to assess general health conditions, blood tests will be required, including complete blood count, prothrombin time, activated partial thromboplastin time and fasting blood glucose. In cases of abnormal findings, the participant will be referred to the physician in order to treat the condition before having the implant insertion surgery done.

##### Surgical and prosthodontic procedures

Antibiotic prophylaxis with 2 g of amoxicillin will be administered 1 h preoperatively [27]. In case of allergy to penicillin, 600 mg of clindamycin will be used. Each patient will then receive a Straumann® Standard Plus SLActive® regular neck implant (Straumann 0.33.051S/052S/053S, Institute Straumann AG, Basel, Switzerland) in the mandibular midline. The implant length will be defined according to the bone height availability, which will be assessed by means of the panoramic and cephalometric radiographs, with the aid of a transparent template. After infiltration anesthesia, incision will be performed using a size 15C disposable scalpel blade. Surgical access will be as conservative as possible, involving a minimal crestal incision, except when a more extensive access is needed for regularization of the alveolar bone crest at the discretion of the surgeon. Drilling sequence and implant insertion will be executed according to the manufacturer’s protocol. The upper denture will serve as a reference guide for the installation of the implant and it will be properly disinfected before surgery with 2 % chlorhexidine digluconate by being soaked in this solution for 10 min [28].

Bone quality and jaw shape will be noted according to the classification proposed by Lekholm and Zarb [29]. Furthermore, final insertion torque will be recorded from the drilling unit with the aid of a manual torque wrench. Implant stability quotient (ISQ) will be assessed using a magnetic resonance frequency device (Osstell Mentor, Integration Diagnostics, Göteborg, Sweden). Final insertion torque will be kept around 20 N.cm and the implant platform placed at least 1 mm above the gingival margin. A healing abutment will be connected and the implant will be allowed to heal for 3 weeks. Sutures will be performed with simple interrupted stitches and removed after 7 days. In addition, the mandibular denture will be relined with a soft acrylic temporary relining material (Soft Comfort, Dencril, São Paulo, Brazil).

Postoperatively, participants will be advised to have a soft food diet and to rinse with a 0.12 % chlorhexidine mouthwash for 1 week. Additionally, paracetamol 750 mg will be provided as the analgesic option to be taken to a maximum of four times daily as needed, since it has been shown to be effective in relieving postoperative pain and has a low incidence of adverse effects [30]. Additional postoperative medication will be prescribed for case-specific situations.

After 3 weeks, the healing abutment will be removed, the gingival collar will be irrigated with 0.12 % chlorhexidine and implant stability will be assessed. Subsequently, a 3.4-mm retentive titanium anchor abutment (Straumann 048.439, Institute Straumann AG, Basel, Switzerland) will be connected and tightened to 35 N.cm with a torque wrench. The temporary relining material will be removed and a space relief will be made in the inner part of the denture to accommodate the abutment and the corresponding elliptical matrix (Straumann 048.456, Institute Straumann AG, Basel, Switzerland). The matrix will be incorporated to the denture using self-curing acrylic resin and the patient will be instructed to keep the upper and lower dentures firmly occluded in the habitual position until the final polymerization of the resin. Occlusion will be checked and, if necessary, adjustments will be made to guarantee a balanced occlusal scheme. No interventions will be performed to the maxillary denture.

### Outcomes

The effectiveness of both treatments will be measured by means of two primary patient-centered outcomes: oral health-related quality of life (OHRQoL) impacts and satisfaction with the dentures:OHRQoL impacts: the cross-culturally adapted Brazilian version of the Oral Health Impact Profile for edentulous subjects (OHIP-EDENT) will be used [31, 32]. It contains 19 items divided into four different subscale domains: (I) masticatory discomfort and disability (four items), (II) psychological discomfort and disability (five items), (III) social disability (five items) and (IV) oral pain and discomfort (five items). The items are answerable on a 3-point Likert scale and responses will be summed to obtain an overall OHIP-EDENT score and for each of the four domains. Higher scores represent worse OHRQoLSatisfaction with the dentures: a 10-cm uninterrupted Visual Analog Scale will be used in order to assess the participants’ ratings of their satisfaction with the upper and lower dentures in relation to the parameters “general satisfaction,” “comfort,” “stability,” “aesthetics,” “ability to speak,” and “ability to chew.” Each participant will indicate their level of satisfaction with each parameter by marking a point along the scale, in which one end signifies “unsatisfied” and the other end signifies “satisfied,” respectively. Then, an assistant will convert each mark into a value of between 0 to 100 by placing a transparent template with numbered intervals from 0 to 100 mm.

Masticatory performance will be assessed as a secondary outcome using a two-colored chewing gum test and a qualitative and quantitative colorimetric method to measure the color-mixing ability [33]. The selected test food will be the Vivident Fruitswing “Karpuz/Asai Üzümü” (Perfetti van Melle, Turkey), a two-colored gum comprising a green and a dark violet layer measuring 43 mm × 12 mm × 3 mm. Participants will be asked to sit upright in a dental chair and to chew the gum on their preferred chewing side for 20 and 50 cycles. The chewed gum will be then retrieved from the oral cavity, placed in a transparent plastic bag and flattened to a 1-mm thick wafer by pressing on a custom-made polyvinyl chloride plate with a milled depression of 1 mm × 50 mm × 50 mm. Each specimen will be labeled with random numbers to allow blind assessment. Both sides of the specimen will be scanned using a flatbed scanner at a resolution of 500 dpi. Visual and electronic analysis of the chewed gum samples will be done according to the classification proposed by Schimmel et al. [33]. Analysis will be made by two investigators blinded to the study groups and treatment stage. ViewGum software (dHAL Software, Kifissia, Greece, www.dhal.com) will be used for electronic colorimetric analysis.

Other clinical outcomes will be recorded in order to provide a comprehensive assessment of the intervention, such as implant survival rate, implant stability quotient, peri-implant bone changes, peri-implant soft tissue aspects and incidence of prosthodontic repair/adjustment events. Control variables, such as age and gender, as well as baseline clinical variables will be recorded for patient description and subgroup data analysis. Subjects will also be classified according to the American College of Prosthodontists’ Index [34].

Table 1 shows all the study outcomes and the time frame for assessment throughout the clinical trial.

**Table 1 Tab1:** Standard Protocol Items: Recommendations for Interventional Trials (SPIRIT) diagram

	Study period						
	Enrollment	Allocation	Post allocation				
Time point	Pretreatment	*t* _0_	Baseline	Implant placement	*t* _1_	*t* _6_	*t* _12_
Enrollment:							
Eligibility screen	x						
Informed consent	x						
Allocation		x					
Interventions:							
Conventional denture (control group)		x	x			x	x
Single-implant mandibular overdenture (SIMO) (intervention group)		x	x	x	x	x	x
Assessments:							
Oral health-related quality of life (OHRQoL)			x			x	x
Satisfaction with dentures			x			x	x
Masticatory performance			x			x	x
Implant stability^a^				x	x		x
Peri-implant bone level^a^					x	x	x
Peri-implant soft tissue health^a^					x	x	x
Prosthodontic events							
Costs							

^a^Assessed only for the single-implant mandibular overdenture (SIMO) group

### Economic analysis

#### Study perspective

A cost-effectiveness analysis will be performed from the health care provider perspective. Cost estimations of the study interventions will be derived from the clinical trial, which is a reproduction of a typical private setting for oral health care in Brazil, since implant treatment is not covered by the public health system and has limited reimbursement from insurance companies. An additional analysis will be performed using the patient perspective, in which costs will be estimated according to the reference pricing of dental procedures and treatments by the Brazilian Dental Association (Classificação Brasileira Hierarquizada de Procedimentos Odontológicos – CBHPO) and reference gross costs will be derived from a panel of specialists.

#### Time horizon and discount rates

The time frame for primary data collection will be 1 year starting from group assignment of each participant of the clinical trial. For modeling-based data, a maximum time horizon of 10 years will be assumed as a relevant time frame for clinical trials, both to accommodate the needs of decision-makers and to provide a “trajectory” of summary measures over time [35]. In this case, both costs and outcomes will be discounted at an annual rate of 5 %, as recommended by Brazilian guidelines [36].

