#### Cost-effectiveness analysis

A cost-effectiveness analysis will be carried out by calculating the incremental cost-effectiveness ratio (ICER), which represents a single, common effect that measures the difference in magnitude between the two alternatives using data retrieved from a clinical trial, expressed in terms of the incremental cost per unit of effect, as follows:$$ ICER=\left(Cos{t}_a-Cos{t}_b\right)/\left( Effectivenes{s}_a- Effectivenes{s}_b\right), $$where the measures of effectiveness will be considered to be the satisfaction with the dentures and the OHRQoL impacts.

Decision analysis will be carried out to model the outcomes of decision between the two alternatives. This analysis considers that the outcomes of decisions are not certain, but that the probabilities of different outcomes are known from the trial-based data. The Markov model with Monte Carlo simulation will be used since the decision analysis problem involves risk that is continuous over time, the timing of events is important, and important events may happen more than once.

Markov models assume that a patient is always in one of a finite number of discrete health states, called Markov states [37]. All events are represented as transitions from one state to another. Important events for this study will be represented in a tree-type diagram that identifies the decision alternatives (decision node), the list of the possible outcomes of each alternative (chance nodes) and the sequence of events (terminal node). The full decision tree will contain all the relevant nodes and the paths between them, as well as the probabilities assigned to chance events and the values attached to each potential final state. Data derived from the clinical trial will be used to construct a Markov decision-tree model of CD versus SIMO, considering the most relevant clinical events, their related probabilities of transitions from one state to another) and estimated costs from each course of action.

One-way sensitivity analysis will be performed to assess the impact that changes in certain parameters (e.g., implant/component costs, time horizon, etc.) will have on the model’s conclusions, as well as to determine which parameters are the key drivers of a model’s results. A tornado diagram will be constructed to show graphically the results of various assumptions on the final outcome in the sensitivity analysis. TreeAge Pro 2014 software will be used for the cost-effectiveness analysis.

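### The 10-year Markov model names the trial as the source of its event probabilities, but one year of follow-up in about 14 people per arm cannot inform years 2-10 and barely estimates rare events

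*Protocol article*

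**What the plan says.** The Protocol article, under Time horizon and discount rates, separates two periods. For the trial itself: "The time frame for primary data collection will be 1 year starting from group assignment of each participant of the clinical trial". For the model: "For modeling-based data, a maximum time horizon of 10 years will be assumed", with costs and outcomes discounted at 5% a year.

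Under Cost-effectiveness analysis, the article explains that outcomes of decisions are uncertain "but that the probabilities of different outcomes are known from the trial-based data". It adds: "Data derived from the clinical trial will be used to construct a Markov decision-tree model of CD versus SIMO", and the same sentence covers the relevant events, their transition probabilities and their costs. Uncertainty is to be explored by Monte Carlo simulation, for which no parameter distributions are given. A one-way sensitivity analysis with a tornado diagram is also planned; its named examples are implant and component costs and the time horizon.

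Under Sample size estimation, the number planned is "a minimum final sample of 28 participants, 14 in each treatment group". Costs are collected over the same 1-year follow-up (Estimation of costs). A panel of specialists is mentioned twice: for reference gross costs (Study perspective) and for instrument and equipment lifespans (Table 2). It is not given a role in event rates.

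**The concern.** The model needs transition probabilities for each of up to ten years, and the only source the article names observes one. The article justifies a Markov model partly by the importance of event timing and by the possibility of repeat events. Timing and recurrence in years 2-10 are exactly what one year of data cannot show. Within year 1, with about 14 people per arm, an uncommon event such as an implant loss will often not be seen at all, and if seen once its rate is almost unconstrained. The article's own Background reports high implant success rates, so very few losses are to be expected.

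At stake is the 10-year incremental cost-effectiveness ratio (ICER) and the tornado diagram built on it. The article offers the longer horizon expressly for decision-makers. If its inputs beyond year 1 have no basis, that result has none either, however carefully the first year is measured.

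**Working it through.** **Inputs from the article.** Follow-up 1 year; model horizon at most 10 years; minimum of 14 per arm; 10% allowance for loss to follow-up on a starting number of 24, that is 12 per arm.

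**The plan's own figure.** 12 × 1.10 = 13.2, and 12 / 0.90 = 13.3; both round up to 14 per arm, 28 in total. The stated 28 is reproduced. The 24 cannot be checked, because no standard deviations are given.

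**Assumption.** The article gives no annual event rates. A range of 1% to 5% per year is used for illustration.

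**Step 1: precision of a first-year probability with n = 14 (exact Clopper-Pearson, two-sided 95%).**

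- 0/14: upper limit 1 − 0.025^(1/14) = 23.2%.
- 1/14 = 7.1%: lower limit 1 − 0.975^(1/14) = 0.2%; upper limit 33.9%.
- 2/14 = 14.3%: limits 1.8% to 42.8%.

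**Step 2: chance of seeing no event, (1 − p)^14, against the true 10-year risk, 1 − (1 − p)^10.**

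| Assumed annual risk p | No event among 14 in year 1 | True 10-year risk |
|---|---|---|
| 1% | 87% | 9.6% |
| 2% | 75% | 18% |
| 3% | 65% | 26% |
| 5% | 49% | 40% |

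With 12 completers per arm, the chance of no event is 89% at 1% and 54% at 5%.

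**Step 3: how many people would be needed.** A 95% chance of at least one event in a year needs n ≥ ln(0.05) / ln(1 − p): 299 per arm at 1%, 149 at 2%, 59 at 5%.

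**Step 4: what a constant-rate extension would give.** The article does not state its extrapolation rule, so this step is conditional. If a first-year proportion were repeated each year:

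- 0/14 gives 0% at 10 years, while its upper limit gives 1 − (1 − 0.232)^10 = 93%.
- 1/14 gives 1 − (13/14)^10 = 52%; its limits give 1 − (1 − 0.0018)^10 = 2% and 1 − (1 − 0.339)^10 = 98%.

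**Step 5: years 2-10.** No arithmetic is needed. Events that begin only after the first year have no chance of being observed, whatever the sample size. For the attachment parts the observed time is shorter still: the clock starts at group assignment, and planning, surgery and three weeks of healing come before the matrix is fitted.

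These calculations count at most one event per person. They suit events such as implant loss better than recurrent maintenance.

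**The case against.** The strongest reply is that this is a condensed article. Extrapolation rules, parameter distributions and the handling of zero counts are commonly left to a full economic analysis plan. The text says trial data will be used to build the model; it does not say only trial data. The sentence with the word *known* can be read as a general description of decision analysis. Ten years is a maximum, the horizon is varied in the sensitivity analysis, Monte Carlo simulation is planned, and a within-trial ICER is already calculated. Fourteen per arm is also a minimum.

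Much of this stands as a limit on the point:

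- A reader might infer that unobserved events will be entered as zero for ten years, or that first-year rates will be repeated unchanged. The article states neither, so Step 4 is only an illustration.
- A reader might infer that the model will favour the overdenture by leaving out its late costs. That does not follow. A single early event could overstate its risk, and missed late events in the conventional-denture arm would lower that arm's costs too.
- The idea that wear, loss and replacement fall mainly after year 1 is plausible, but no figure in the article supports it.
- Frequent events are better estimated for year 1. For example, 7/14 is 50% with limits of 23% to 77%.

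The reply does not remove the point. The article is not silent about the source: it names the trial for the probabilities. Varying the horizon exposes reliance on later years but supplies no rates for them. Monte Carlo simulation around first-year estimates would spread first-year uncertainty only. A modest increase over 14 would not reach the 59 to 299 in Step 3, and no sample size turns one year of follow-up into ten.

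**Conclusion.** The concern holds in this form: the article assigns to the trial a set of model inputs that the trial cannot supply. For years 2-10 it provides no information. For rare events in year 1 the information is very weak: 0/14 leaves annual risks up to 23% open, and events with an assumed annual risk of 1-5% are missed with probability 87-49% although their 10-year risk is about 10-40%. Describing such probabilities as known is not warranted.

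The sizes rest on the planned minimum of 14 per arm, on one event per person and on the assumed annual rates; the 10-year risks also take the annual rate as constant. The direction and size of the effect on the 10-year ICER cannot be determined from the article. The 1-year comparison of quality of life and satisfaction, and the within-trial ICER, are not affected. The wording should be corrected before the model is built.

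**What to change.** In the sections on time horizon and on cost-effectiveness analysis:

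1. Use trial-based transition probabilities for year 1 only.
2. For years 2-10, take time-dependent event rates and component and denture lifetimes from published longer-term studies or expert elicitation, each with a stated range. Elicitation would extend the specialist panel's present role and should be described as such.
3. State the extrapolation rule.
4. Give every probability a distribution that does not fix an unobserved event at zero (a beta distribution, for example), and run a probabilistic sensitivity analysis alongside the one-way analysis.
5. Say that the probabilities are *estimated* from the trial rather than *known* from it.
6. Report the 10-year result as a scenario analysis beside the already planned within-trial 1-year ICER.

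The cost is a change of wording and some literature and modelling work, with no new patients or visits. The 10-year result will look less precise.
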